### Eligibility criteria

3.3

Inclusion criteria:

1) The diagnostic criteria of potential participants refer to the 2015 Institute of Medicine (IOM) criteria for CFS (Clayton, 2015):

Substantial reduction or impairment in activity level with fatigue >6 months,Post-exertional malaise (PEM),Unrefreshing sleep,One of the symptoms: cognitive impairment or orthostatic intolerance.

2) Age 20–60 years, of either sex, and right-handed.3) No use within the past month of treatments considered likely to affect the primary outcomes or mechanistic assessments, including herbal formulas, acupuncture, other related non-pharmacological therapies, and antibiotics, probiotics, or prebiotics.4) Able to communicate and complete study questionnaires, and willing to accept randomization and provide written informed consent.

Exclusion criteria:

Fatigue symptoms that do not lead to a substantial reduction in the capacity for work, education, social and recreational activities, or activities of daily living.Severe comorbid conditions, including decompensated cardiac, cerebrovascular, hepatic or renal disease, malignancy, active infection, or neurological disorders.Severe psychiatric disorder, or severe depressive symptoms requiring immediate treatment, as indicated by a Self-Rating Depression Scale score ≥63 or clinical judgment.Pregnancy, planned pregnancy or lactation.Contraindications to MRI, such as pacemaker, neurostimulator, metallic implants or insulin pumps, in participants enrolled in the imaging substudy.Morbid obesity, defined as BMI > 45 kg/m^2^.Any other condition that, in the opinion of the investigator, would contraindicate participation or continuation in the trial, or would provide a more likely alternative clinical explanation for fatigue.

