### Statistical analysis

3.9

Statistical analyses will be performed using SPSS version 26.0 (IBM Corp., Armonk, NY, USA). Baseline characteristics will be summarized as mean (SD) or median (IQR) for continuous variables and as number (%) for categorical variables, as appropriate. Longitudinal outcomes will be analyzed using linear mixed-effects models including fixed effects for group, time, and group-by-time interaction. The models will be adjusted for baseline outcome values, study center, and sex, with additional prespecified covariates included where appropriate. For the primary outcome analysis, baseline FS-14 score will be included as a covariate. Secondary clinical outcomes will be interpreted with consideration of multiplicity, and exploratory omics and imaging analyses will be interpreted as hypothesis-generating. All tests will be two-sided, and a *p* value <0.05 will be considered statistically significant. The primary efficacy analysis will follow the intention-to-treat principle. A per-protocol analysis will be conducted as a sensitivity analysis. The primary comparison will be the between-group difference in change in FS-14 total score from baseline to week 8, estimated from the mixed-effects model. Missing data will be handled under the missing-at-random assumption inherent to mixed-effects models, and additional sensitivity analyses will be conducted if warranted. Because this is a multicenter trial, study center will be included in the analysis model to account for potential between-center variability. All statistical analyses will be performed with group allocation concealed until database lock. The full trial protocol is provided in this article and its online Supplementary materials.

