### Metabolomics and microbiota analyses

3.10

These analyses are exploratory and hypothesis-generating, are not formally powered for confirmatory inference, and will be interpreted primarily as effect-size estimation and biological signal characterization rather than definitive hypothesis testing. These findings will not be interpreted as confirmatory efficacy evidence. Targeted metabolomics data will be analyzed using multivariate and univariate approaches to identify differential metabolites, with particular focus on the tryptophan pathway. Multivariate analyses will include principal component analysis and supervised discrimination methods, whereas univariate comparisons will be corrected for multiple testing using the false discovery rate (FDR). Pathway enrichment analyses will then be performed, and associations between metabolite changes and clinical outcomes will be examined using Pearson or Spearman correlation analyses, as appropriate.

Microbiota data will be analyzed at the levels of alpha diversity, beta diversity, and differential taxonomic abundance. Alpha diversity indices will be compared using appropriate parametric or nonparametric methods according to data distribution and study design. Beta diversity will be assessed using permutational multivariate analysis of variance, and differentially abundant taxa will be identified using FDR-controlled methods. Associations between microbial features and clinical measures will be explored using multivariable regression and ordination-based approaches, as appropriate.

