Beyond evaluating clinical effectiveness, the present study is intended to explore a biologically informed mechanistic framework for CFS. To our knowledge, this integrative design distinguishes the present protocol from most previous CFS trials, which have generally focused on clinical outcomes alone. This trial is also designed as an exploratory mechanistic study focusing primarily on the tryptophan-kynurenine pathway as a candidate link between gastrointestinal disturbance and central symptom expression in CFS. Increasing evidence implicates neuroendocrine–immune dysregulation and the gut-brain axis in CFS, but the relevant causal pathways remain poorly defined. Previous studies have reported altered tryptophan metabolites in cerebrospinal fluid and peripheral samples from patients with CFS, while clinical and microbiome studies have consistently noted gastrointestinal complaints and gut dysbiosis (Walitt et al., 2024; Leong et al., 2022; Gao et al., 2020). Because tryptophan and its downstream catabolites lie at the interface between gut microbial activity, immune signaling, and central nervous system function, the tryptophan–kynurenine pathway represents a biologically plausible focal mechanism linking peripheral disturbance with fatigue-related symptoms. We therefore selected plasma and stool tryptophan-pathway metabolites as the primary exploratory mechanistic domain.

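### The metabolite-to-symptom association in section 3.10 is fixed as a simple correlation with no arm term, although arm may move both variables and adjustment needs no new data

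*Protocol article*

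**What the plan says.** Section 3.10 (Metabolomics and microbiota analyses) plans, for the metabolites, principal component analysis, supervised discrimination, and univariate comparisons with false discovery rate (FDR) control. For the link to symptoms it states: "associations between metabolite changes and clinical outcomes will be examined using Pearson or Spearman correlation analyses, as appropriate". No other method is named for that link.

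For the microbiota the same section states: "Associations between microbial features and clinical measures will be explored using multivariable regression and ordination-based approaches, as appropriate". Its group comparisons are described as "Alpha diversity indices will be compared using appropriate parametric or nonparametric methods according to data distribution and study design" and "Beta diversity will be assessed using permutational multivariate analysis of variance".

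The Discussion ranks the domains. It selects "plasma and stool tryptophan-pathway metabolites as the primary exploratory mechanistic domain" and places metagenomics and imaging second. Section 3.9 describes the mixed models for longitudinal outcomes: "The models will be adjusted for baseline outcome values, study center, and sex, with additional prespecified covariates included where appropriate". Neither section says whether that adjustment extends to the metabolite or diversity comparisons.

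Plasma and stool are sampled at baseline and week 8 (section 3.7.3, Table 1), and randomisation is stratified by centre (section 3.5).

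**The concern.** Section 2.4 hypothesises that Tuina improves fatigue more than usual care does, and that the improvement may go with altered tryptophan metabolites. The Discussion adds that the control programme may itself influence fatigue and possibly gut-related measures. On the protocol's own account, then, arm could be a common cause of both variables being correlated.

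In that case a correlation over all participants is non-zero even if, within each arm, the participants whose metabolites change most are no more likely to improve. A multiplicity correction does not remove this, because it is a shift in the quantity being estimated and not chance. It matters for the intended use: the Discussion hopes for candidate biomarkers and responder profiles, and these need a link between participants within an arm.

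The domain ranked first has the method that cannot carry an arm term, while a lower-ranked domain has one that can. The article gives no reason for this.

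A second, smaller matter is precision. Section 3.10 names effect-size estimation as its main purpose, and using the baseline sample as a covariate gives tighter group estimates than a change score.

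**Working it through.** **Inputs from the protocol (section 3.4).** FS-14 difference 1.60, SD 3.28, two-sided alpha 0.05, power 80%, 66 per group, 20% dropout, 83 per group (166 in total).

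**The plan's own figure.** n per group = 2 × (1.960 + 0.842)² × 3.28² / 1.60² = 2 × 7.85 × 4.2025 ≈ 66. Then 66 / 0.80 = 82.5, rounded up to 83, or 166 in total. Both figures reproduce. The standardised FS-14 effect is d1 = 1.60 / 3.28 = 0.488, and the completers number 2 × 66 = 132.

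**Assumptions.** The documents give no metabolite effect, so the shift d2 is varied from 0 to 1.0 SD. The arms are pooled and equal in size, the data are normal, and the within-arm correlation is set to zero.

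**Induced correlation.** r = (d1/2)(d2/2) / √[(1 + d1²/4)(1 + d2²/4)], in absolute value. For example, at d2 = 0.5: 0.244 × 0.25 / √(1.0595 × 1.0625) = 0.0610 / 1.061 = 0.057.

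**Rejection rates.** The table gives the share of 20,000 simulated trials per setting in which a nominal 5% Pearson test rejects.

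| d2 (SD) | induced r | pooled, N = 132 | arm-adjusted, N = 132 | pooled, N = 166 |
|---|---|---|---|---|
| 0 | 0.000 | 4.9% | 5.1% | 4.9% |
| 0.2 | 0.024 | 6.0% | 5.1% | 6.0% |
| 0.3 | 0.035 | 6.8% | 5.0% | 7.4% |
| 0.5 | 0.057 | 10.3% | 5.1% | 11.2% |
| 0.8 | 0.088 | 17.5% | 5.0% | 20.3% |
| 1.0 | 0.106 | 22.9% | 5.2% | 27.6% |

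With 166 participants the arm-adjusted test rejects in 4.8% to 5.3% of trials. The pooled rates are false positives only for a within-arm link, because the overall correlation really is non-zero in these settings. Only Pearson was simulated.

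**Baseline adjustment.** With equal variances and baseline to week 8 correlation ρ, which is assumed, the variance of the group difference is proportional to 1 − ρ² with baseline as a covariate and to 2(1 − ρ) for a change score. The ratio is (1 + ρ)/2:
- ρ = 0.3: 0.65
- ρ = 0.5: 0.75
- ρ = 0.7: 0.85

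**The case against.** The strongest reply is that section 3.10 is exploratory by its own statement: the analyses are unpowered and are not to be read as confirmatory evidence of efficacy. No efficacy conclusion depends on them. Section 2.3 asks only whether improvement is accompanied by biological change, and a correlation across all participants is a fair answer to that loose question. This stands, and it limits the weight of the point.

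Several stronger readings are tempting, and the documents do not support them:
- **That the whole section rests on simple correlations.** It does not. Microbial associations get multivariable regression, PERMANOVA can hold covariates, and the alpha-diversity test follows the study design.
- **That the group comparisons are unadjusted, or that the arms are certainly pooled.** The text is silent on both. Univariate is set against multivariate and can simply mean one metabolite at a time. Section 3.9 could be read to cover outcomes measured twice, and an analysis plan that is not shown may settle it.
- **That week 8 samples exposed to antibiotics or probiotics would go unnoticed.** The entry criterion on "and antibiotics, probiotics, or prebiotics" covers only the month before enrolment, but Table 1 records concomitant medications at every visit from week 0. Only the use of those records in this analysis is unstated.
- **That the aim is a within-person association.** Section 2.3 does not say so, and a regression of change on change also compares participants.
- **That centre biases the comparison of arms.** Stratified randomisation balances centre across arms, and nothing in the documents gives a size for a correlation created by centre.

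What remains is a method that the article does state. The supplement references in sections 3.7.3 and 3.11 concern laboratory, sequencing, bioinformatic and imaging methods, not the statistics of this association.

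**Conclusion.** The point holds for the metabolite association. Section 3.10 names a method without an arm term, in the leading mechanistic domain, where the protocol expects arm to act on both variables. The effect is modest: an induced r of about 0.02 to 0.11, and 6% to 23% apparent within-arm findings at 132 completers, against about 5% with an arm term. These figures rest on pooled arms, the planned FS-14 effect, assumed metabolite shifts of 0.2 to 1.0 SD and usable samples from all 132 completers. If Tuina does not move the metabolite, or if the correlations are run within arms, the problem disappears.

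For the group comparisons this is a clarification and not an error. If change scores were used, covariate adjustment would bring the variance to 0.75 to 0.85 of that at ρ of 0.5 to 0.7. The trial's primary result is unaffected. This is an inexpensive improvement to an exploratory analysis.

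**What to change.** In section 3.10:

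1. Replace the Pearson or Spearman sentence with a regression of clinical change on metabolite change, adjusted for arm, both baseline values and centre, or with the equivalent partial correlation. Keep the hypothesis-generating label.
2. State that the one-metabolite-at-a-time and alpha-diversity group comparisons use the section 3.9 adjustment, that is, week 8 value on baseline value, group, centre and sex, with FDR control applied to the group terms.
3. Optionally, add a sensitivity analysis without week 8 samples from participants with recorded on-study antibiotic or probiotic use.

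The cost is wording only. Baseline samples, centre, sex and concomitant medications are already collected, and the sample size does not change.

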### Imaging preprocessing and analysis

3.11

Imaging data will be processed using a standardized pipeline in MATLAB with SPM12- and DPABI-based tools. The first 10 volumes of each run will be discarded to allow for signal stabilization. Preprocessing will include slice-timing correction, realignment for head-motion correction, coregistration to each participant’s structural T1-weighted image, normalization to Montreal Neurological Institute space, resampling, and spatial smoothing. Structural images will be segmented into gray matter, white matter, and cerebrospinal fluid and normalized using established procedures. Nuisance regression will include motion parameters and signals from white matter and cerebrospinal fluid, followed by detrending and band-pass filtering. Volumes exceeding predefined motion thresholds will be censored, and participants exceeding prespecified motion criteria will be excluded. The specific thresholds for framewise displacement, translational/rotational motion, and participant exclusion are provided in the online Supplementary materials. Detailed MRI acquisition parameters, preprocessing procedures, motion criteria, and quality-control steps are provided in the online Supplementary materials.

### Data management and monitoring

3.12

CRFs will be completed by trained study staff. Two independent data managers, blinded to treatment allocation, will perform double data entry and verify the study database. Source documents will be stored securely at the study site, and electronic data will be maintained on password-protected servers with role-based access control. Participant confidentiality will be protected by assigning unique study identification numbers and storing personal identifiers separately from research data. Only de-identified, aggregate data will be reported in publications. Shuguang Hospital Affiliated to Shanghai University of Traditional Chinese Medicine will serve as the coordinating site and will be responsible for overall trial coordination and protocol implementation. Safety oversight will be provided by the registered Data and Safety Monitoring Committee in accordance with institutional requirements. Quality assurance procedures will include site training, standardized operating procedures, regular instrument calibration, and periodic monitoring. Intervention fidelity will be supported through standardized therapist training, treatment logs, and periodic checks of protocol adherence. Treatment records will document session completion, adherence to standardized procedures, and any protocol-related variations identified during the trial. Participant adherence will be monitored by recording session attendance and reasons for missed visits and will be supported through reminder contacts and flexible scheduling within protocol limits. Lifestyle-related information that may influence microbiome and metabolic profiles, including major changes in dietary habits, physical activity patterns, and other relevant health behaviors, will be recorded when applicable. No formal interim efficacy analyses are planned. The Data and Safety Monitoring Committee may recommend trial modification or termination in the event of unacceptable safety concerns, major protocol violations, or other circumstances that materially affect participant safety or trial feasibility.

## Discussion

4

A central challenge in the management of CFS is the lack of effective and scalable non-pharmacological therapies. To address this gap, we designed a superiority trial with blinded outcome assessment and prespecified analyses, comparing standardized Tuina with standardized usual care. Accordingly, this design is intended to compare the effects of standardized Tuina with those of standardized usual care in a clinically relevant setting, while also allowing assessment of the durability of any treatment effects over a 24-week follow-up period. At the same time, because the standardized usual care condition includes lifestyle counselling and symptom-oriented support, it may itself influence fatigue-related symptoms and, potentially, gut-related measures. Therefore, any between-group differences should be interpreted as the comparative effect of standardized Tuina versus standardized usual care, rather than as the isolated effect of Tuina against an inert control. In addition, the open-label nature of the trial should be considered when interpreting patient-reported outcomes. Because participant and therapist blinding is not feasible in this type of manual therapy study, the primary outcome (FS-14) and several secondary outcomes (including PSQI, SAS, and SDS) rely on self-reported assessments and may therefore be influenced by expectation effects, reporting bias, and participants’ awareness of treatment allocation. While blinded outcome assessment, standardized data handling, and prespecified statistical analysis plans have been implemented to reduce detection and analytical bias, these procedures cannot fully eliminate bias inherent to subjective outcome reporting in an open-label design. Accordingly, interpretation of these outcomes should be made with appropriate caution.

Beyond evaluating clinical effectiveness, the present study is intended to explore a biologically informed mechanistic framework for CFS. To our knowledge, this integrative design distinguishes the present protocol from most previous CFS trials, which have generally focused on clinical outcomes alone. This trial is also designed as an exploratory mechanistic study focusing primarily on the tryptophan-kynurenine pathway as a candidate link between gastrointestinal disturbance and central symptom expression in CFS. Increasing evidence implicates neuroendocrine–immune dysregulation and the gut-brain axis in CFS, but the relevant causal pathways remain poorly defined. Previous studies have reported altered tryptophan metabolites in cerebrospinal fluid and peripheral samples from patients with CFS, while clinical and microbiome studies have consistently noted gastrointestinal complaints and gut dysbiosis (Walitt et al., 2024; Leong et al., 2022; Gao et al., 2020). Because tryptophan and its downstream catabolites lie at the interface between gut microbial activity, immune signaling, and central nervous system function, the tryptophan–kynurenine pathway represents a biologically plausible focal mechanism linking peripheral disturbance with fatigue-related symptoms. We therefore selected plasma and stool tryptophan-pathway metabolites as the primary exploratory mechanistic domain.

Fecal metagenomic profiles and central network measures assessed by resting-state fMRI and MRS will be treated as secondary exploratory domains intended to contextualize any observed biochemical changes. This hierarchical design is intended to reduce interpretive overreach while still allowing assessment of broader gut-brain features that may be relevant to symptom improvement. This approach also reflects the differing levels of prior biological plausibility and measurement maturity across the exploratory domains. In addition, evidence from related conditions and mechanistic studies suggests that Tuina, as an external manual therapy, may influence parasympathetic activity (Goldenberg and Kalichman, 2024; Henley et al., 2008), gastrointestinal function (Geng et al., 2020; Stringer et al., 2008), microbial ecology (Sachula et al., 2024), and may also modulate brain processes relevant to fatigue, pain, and mood (Wu et al., 2023; Ma et al., 2023). However, these pathways should be regarded as biologically plausible candidate mechanisms rather than established causal effects in CFS. In this respect, the integration of omics-based and neuroimaging-based measures may help generate candidate biomarkers and responder profiles for future studies.

In summary, this study is designed not only to provide higher-quality clinical evidence for Tuina in CFS, but also to serve as a mechanistic pilot examining associations between symptom change and alterations in tryptophan metabolism, gut microbial features, and brain functional characteristics. If the trial demonstrates clinically meaningful improvement together with convergent exploratory biomarker changes, the findings will provide preliminary support for larger multicenter confirmatory studies and help refine mechanistic hypotheses regarding Tuina in CFS, particularly with respect to gut-related symptoms and gut-brain mechanisms. At the same time, the exploratory nature of the omics and imaging analyses means that these findings should be interpreted as hypothesis-generating rather than definitive evidence of causality.
